## Abstract

**Background:**

Despite adequate treatment, up to 30% of treated antihypertensive patients with primary, uncomplicated hypertension remain uncontrolled. We proposed that high intracellular activity of the ATP regenerating enzyme creatine kinase (CK) increases pressor responses and hypertension risk. In line with this, we found that plasma CK activity after rest, a surrogate measure of tissue activity, is the main predictor of blood pressure levels and failure of antihypertensive therapy in the general population. In addition, the creatine analog and competitive oral creatine kinase inhibitor beta-guanidinopropionic acid effectively and safely reduced blood pressure in the spontaneously hypertensive rat. However, to our knowledge there are no human data on the safety of oral supplementation with this substance. Therefore, we will assess the tolerability of beta-guanidinopropionic acid in men, compared to creatine and placebo.

**Methods/Design:**

This is a randomized, active and placebo controlled, triple blind, double dummy, single center clinical intervention trial in 24 healthy male volunteers, 18 to 50 years old, recruited in the Netherlands. The intervention consists of one week of daily oral administration of beta-guanidinopropionic acid 100 mg, creatine 5 gram, or placebo. The primary outcome is the tolerability of beta-guanidinopropionic acid as a descriptive measure, in an intent-to-treat analysis. Other outcomes include the placebo-adjusted differences with baseline in biochemical and hemodynamic parameters, including plasma markers of muscle tissue damage, urine sodium excretion, resting sitting systolic and diastolic brachial blood pressure, supine systolic and diastolic central blood pressure, pulse wave velocity and augmentation index, heart rate, cardiac contractility, cardiac output, and total peripheral resistance.

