### Study design

We wrote the protocol using the SPIRIT '(Standard Protocol Items: Recommendations for Interventional Trials)' recommendations and the 'Template for Intervention Description and Replication (TIDieR) checklist' [33,34].

The ABC trial is a randomized, placebo and active controlled, double-dummy, participant, intervention provider, and outcome assessor (triple) blinded, parallel group, single center (Academic Hospital of the University of Amsterdam), exploratory trial, with three arms: a primary outcome of tolerability of GPA, in comparison with creatine and placebo.

Randomization will be performed by an independent party, the Clinical Pharmacy Unit of the Academic Hospital of the University of Amsterdam, using a computer-generated, nonadaptive, and restricted randomization scheme and a 1:1:1 allocation ratio. The Pharmacy will generate the random allocation sequence. All participants who give consent for participation and who fulfill the inclusion criteria will be randomized to receive GPA 100 mg and creatine placebo matching active creatine 5 gram; creatine 5 gram and GPA placebo matching GPA 100 mg; or double dummy placebo over 1 week. The participant will receive the blinded, randomized trial supplements from the pharmacy. Allocation concealment will be ensured, as the pharmacy will store the allocation list and not release the randomization code until all outcome measures have been assessed and the data bank has been closed. Thus, randomization will be conducted without any influence of the investigators, outcome assessors, or participant characteristics. After assignment to interventions, trial participants, trial staff, and the outcome assessor will remain blinded to whether the participant was given a placebo or a supplement until after all outcome data have been assessed. Data analysis will be performed unblinded. We prespecified the use of accumulating data to decide whether to stop the trial early, in case of serious or unexpected side effects. Independent monitoring visits will take place before the start of the trial, within 1 month after initiation or after inclusion 5th subject; within 2 months after initiation or after inclusion 15th subject; after last patient last visit; and after the data have been entered into the database. Data entry will be verified by two independent researchers. Budget administration is by an independent organization (AMC Research BV, Amsterdam, the Netherlands).

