### Statistical analysis

#### Study outcomes

The primary outcome is the tolerability of GPA after oral administration in healthy male volunteers versus placebo as a descriptive measure, in an intent-to-treat analysis. Other outcomes are to compare the tolerability of GPA with creatine, and differences in hemodynamic and biochemical parameters between treatment arms.

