#### Sample size calculation

This is a first-in-man study with GPA, with allometric data available from other species. According to the European Medicines Agency (EMEA) guidelines [36], we will include eight subjects in each arm, to assess the tolerability of GPA versus placebo and creatine over one week.

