### Recruitment strategy

We will utilize two primary resources for identifying and recruiting potential subjects: advertising and identification in our Healthy Volunteer Research Database. The advertisement has prior approval of the MERC. A dedicated trial staff member will respond to inquiries about participation in the trial on the same day, using a participant information letter approved by the MERC. Screening will continue until the target population is achieved (24 subjects). The enrollment period is planned to extend over 9 months, until December 2014.

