### Electrocardiography and Hemodynamics

On Day 0 (baseline), 1 (in the first hour after intake trial supplements), 2 (after 1 day of trial supplements), and 8 (after 7 days of trial supplements) of the intervention period, we will measure sitting brachial systolic and diastolic blood pressure with an Omron M4 oscillometric device (Omron Healthcare Europe BV, Hoofddorp, the Netherlands) after 5 minutes of rest with an adjusted cuff size on the left arm, at heart level. In addition, we will perform electrocardiography (MAC 5000 Resting ECG System; GE Healthcare; Boston, MA) and ambulatory 24-hour blood pressure monitoring (Spacelabs 90217 Ambulatory Blood Pressure Monitor, Spacelabs Inc. Redmond, WA, USA). Furthermore, at baseline, Day 2, and Day 8, we will estimate central blood pressure, pulse wave velocity, and the augmentation index with an Arteriograph (Tensiomed Kft, Budapest, Hungary); and heart rate, cardiac contractility, cardiac output, and total peripheral resistance using a Nexfin BMEYE, (Amsterdam, the Netherlands) blood-pressure monitor for continuous noninvasive finger arterial blood pressure measurement.

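### Haemodynamic and biochemical outcomes are worded as placebo-adjusted change from baseline in one place and as differences between arms in another, neither with the baseline value as covariate; with 8 men per arm, adjustment is usually more precise

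*Protocol article*

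**What the plan says.** The abstract (Methods/Design) states the effect measure: "Other outcomes include the placebo-adjusted differences with baseline in biochemical and hemodynamic parameters". The Study outcomes section describes the same outcomes only as "differences in hemodynamic and biochemical parameters between treatment arms", without saying whether the scale is the follow-up value, the change, or an adjusted value. Neither place names the baseline value as a covariate or names a model.

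These outcomes serve the secondary (haemodynamic) and tertiary (biochemical) aims in the Objectives section, where GPA is compared with both creatine and placebo. They are not primary: "The primary outcome is the tolerability of GPA after oral administration in healthy male volunteers versus placebo as a descriptive measure".

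On size and allocation, the Sample size calculation section says "we will include eight subjects in each arm, to assess the tolerability of GPA versus placebo and creatine over one week". The Study design section describes a "restricted randomization scheme and a 1:1:1 allocation ratio" and adds that "randomization will be conducted without any influence of the investigators, outcome assessors, or participant characteristics", so no stratification on baseline values is described.

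Baseline values will be available. For example, "at baseline, Day 2, and Day 8, we will estimate central blood pressure, pulse wave velocity, and the augmentation index with an Arteriograph". Brachial pressure is taken at Day 0 and on Days 1, 2 and 8. Most laboratory tests are repeated after 1 and 7 days. Platelet aggregation is repeated at Day 8 only, and TSH, aPTT and PT are not repeated.

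**The concern.** Subtracting the baseline value assumes in effect that a baseline difference between arms carries over in full to follow-up. When rho is below 1 it carries over only in part, so the change score over-corrects: an arm that happens to start high will tend to show a larger fall. With 8 men per arm and no stratification on these measurements, chance differences at Day 0 can be sizeable, and many variables are measured.

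What is at stake is the precision of the trial's haemodynamic and biochemical comparisons, and how they read once the baseline means are seen. The Discussion says that the low dose limits the study of efficacy. Any effects may therefore be small, and avoidable noise matters more.

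**Working it through.** **Inputs from the article.** Eight per arm (Sample size calculation); three arms at 1:1:1 (Study design); 24 in total (Recruitment strategy). Check: 3 × 8 = 24, as stated. The article gives no SD, effect size, power or correlation for these outcomes, so there is no power figure to reproduce.

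**Assumptions.** Equal SD at baseline and follow-up and across arms, a linear relation, and rho between 0.3 and 0.95. Results are in SD units.

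**Step 1: chance imbalance.** The SE of the baseline difference between two arms is SD × √(2/8) = 0.50 SD. The probability of a difference above 0.5 SD in either direction is P(|Z| > 1) = 0.317, about 32% for each variable.

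**Step 2: effect on the change score.** If the arms differ by d at baseline and the true effect is τ, the expected follow-up difference is τ + rho × d. The expected change-score difference is τ + rho × d − d = τ − (1 − rho) × d. For d = 0.5 SD the size of the shift is:
- rho 0.5: 0.5 × 0.5 = 0.25 SD
- rho 0.7: 0.3 × 0.5 = 0.15 SD
- rho 0.9: 0.1 × 0.5 = 0.05 SD

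Averaged over randomisation, d is zero and so is the shift.

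**Step 3: precision.**
- Change score: variance = (2/8) × 2 × SD² × (1 − rho), on 24 − 3 = 21 df.
- Baseline-adjusted (ANCOVA): variance = (2/8) × SD² × (1 − rho²) × (1 + 1/19), on 20 df. The 19 is 24 − 3 − 2, and the last factor is the price of estimating the slope.
- Ratio, ANCOVA to change: (1 + rho)/2 × 20/19.

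| rho (assumed) | SE change | SE ANCOVA | Variance ratio | Ratio of 95% CI half-widths |
|---|---|---|---|---|
| 0.3 | 0.592 | 0.489 | 0.68 | 0.83 |
| 0.5 | 0.500 | 0.444 | 0.79 | 0.89 |
| 0.6 | 0.447 | 0.410 | 0.84 | 0.92 |
| 0.7 | 0.387 | 0.366 | 0.89 | 0.95 |
| 0.8 | 0.316 | 0.308 | 0.95 | 0.98 |
| 0.9 | 0.224 | 0.224 | 1.00 | 1.00 |
| 0.95 | 0.158 | 0.160 | 1.03 | 1.02 |

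The half-width column uses t on 20 and 21 df. Break-even on variance is rho = 2 × 19/20 − 1 = 0.90; on interval width it is about 0.89. To match ANCOVA with 8 per arm, a change score would need 8/0.789 = 10.1 per arm at rho 0.5, 8.9 at 0.7 and 8.4 at 0.8.

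**Step 4: simulation.** With 100,000 simulated trials at each rho, the variance ratios were 0.685, 0.790, 0.840, 0.897, 0.948, 0.999 and 1.024, in agreement with the table. The change-score estimate correlated with the baseline imbalance at −0.50 (rho 0.5), −0.38 (0.7) and −0.22 (0.9). The ANCOVA estimate correlated at about zero.

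**Step 5: is the stated outcome compatible with adjustment?** If follow-up = a + τ × arm + b × baseline, then change = a + τ × arm + (b − 1) × baseline. The treatment estimate τ is the same. Change from baseline can therefore remain the outcome, with the Day 0 value added as covariate.

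**The case against.** The strongest reply is that the abstract names an effect measure, not a model. Step 5 shows that the measure is compatible with adjustment, and a condensed article may leave covariates to a fuller document. This stands in part. A reader might infer that the trial is committed to an unadjusted change-score analysis. The article does not say so: adjustment is neither planned nor ruled out, and the absence of a model is not itself the point. What remains is that the article does state a measure, states it in two different ways, and the more specific wording, taken literally, is usually the less efficient statistic.

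A reader might also infer that the change score gives a wrong answer. It does not, because it is unbiased over randomisation. The shift in step 2 is conditional on the imbalance actually seen.

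Nor is the gain in precision guaranteed. It depends on a correlation that the article does not give. It is only 5% of variance at rho 0.8, nil at 0.9 and slightly negative above that. Same-person measurements taken a few days apart may correlate highly for some variables. Adjustment also removes only the linear effect of that variable's own baseline, not imbalance in other factors.

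Finally, a blanket rule would not fit the schedule, since some tests are repeated once or not at all. A common slope is also doubtful for plasma GPA, whose natural level runs from trace amounts to 1.40 μmol/L (Test product section) and which only one arm receives. Both points stand and limit the fix.

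**Conclusion.** The point holds as a modest improvement in method and wording, not as an error. If the abstract is followed literally, the comparison is less precise than a baseline-adjusted one for rho below about 0.9: about 21% more can be taken off the variance at 0.5, 11% at 0.7 and 5% at 0.8. If rho is 0.95, adjustment costs about 3%. A 0.5 SD imbalance, exceeded in about 32% of trials for each variable, shifts the change-score estimate by 0.05 to 0.25 SD for rho from 0.9 down to 0.5.

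These figures rest on the assumed correlations, equal SDs and linearity. It would be too strong to infer that the trial's main conclusion is at risk. The trial is described as exploratory, its primary outcome is descriptive tolerability, and the sample size was set for that outcome. Only secondary and tertiary estimates are affected.

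**What to change.** Use the same wording in the abstract and in the Study outcomes section, for example:

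*For each continuous haemodynamic or biochemical outcome measured at Day 0 and repeated, the change from Day 0 at each scheduled later time will be compared between arms in a linear model with arm and the participant's own Day 0 value as covariate. Adjusted differences between GPA and placebo, and between GPA and creatine, will be reported with 95% confidence intervals.*

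The later times should follow the measurement schedule of each variable, for example Day 8 only for platelet aggregation. Tests that are not repeated fall outside the rule. Plasma and urine GPA and creatine, where dosing drives the later level, may stay descriptive. Unadjusted changes can still be tabulated.

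No new data are needed, because the Day 0 values are already planned. The cost is a change of wording, one residual degree of freedom (20 instead of 21), and a small loss of precision for any variable whose correlation exceeds about 0.9.

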**Discussion:**

There is an unfulfilled need for new conservative options to treat resistant hypertension. This study will provide first-in-men data on creatine kinase inhibition as a potential new class of antihypertensive drugs.

**Trial registration:**

The Netherlands National Trial Register Trialregister.nl (identifier NTR 4444), registered 9 March 2014.

## Background

Blood pressure reduction may be challenging despite the availability of several classes of antihypertensive drugs [1-5]. A substantial proportion of treated hypertensive patients, up to 30% or more does not achieve blood pressure control. Risk factors for poor control include obesity, age, African ancestry, the presence of diabetes or end organ damage; but non-adherence of the patient, the white-coat effect, therapeutic inertia of the physician, or the concomitant use of blood pressure increasing drugs may also contribute. However, a subgroup of patients with uncomplicated, primary hypertension remains who are uncontrolled despite adequate use of antihypertensive drugs [1-5]. The underlying pathophysiology in these patients is thought to be refractory to currently available drugs, causing early heart disease, stroke, and early mortality. Hence, the current scientific challenge is to develop new conservative options to lower blood pressure [1-5].

We showed in a random, multi-ethnic population sample that plasma CK activity after rest, a surrogate measure of tissue CK, is the main predictor of blood pressure, with a crude increase in blood pressure of 14 mm Hg systolic and 8 mm Hg diastolic per log CK increase [6]. Although plasma and tissue CK activity were found to be higher in men, subjects of African ancestry, and obese patients [6,7], the association was independent of sex, body mass index (BMI), or ethnicity. Therefore, we proposed that high tissue CK might increase pressor responses [6].

Cytosolic CK is tightly bound in the immediate proximity of ATP-utilizing enzymes such as Na^+^/K^+^-ATPase, Ca^2+^-ATPase, and myosin ATPase. Here, ATP synthesized by CK is preferentially used to fuel highly energy-demanding processes such as sodium retention, cardiovascular contractility, as well as remodeling of arteries, promoting hypertension [6,8]. Importantly, in accord with a causal relationship, high tissue CK preceded hypertension in animal models [9,10], as was found with high plasma CK in humans [11], and inhibition of intracellular CK substantially inhibited human vascular contractility *in vitro* [12]. Furthermore, vascular CK gene expression was strongly associated with clinical blood pressure in humans [13], and high plasma CK was found to be the main predictor of failure of antihypertensive therapy in the general population [5,14]. Finally, we recently showed in a randomized control trial of 16-week-old male spontaneously hypertensive rats versus controls (n = 16), that oral CK inhibition with the competitive CK inhibitor beta-guanidinopropionic acid (GPA) 3%, added to rat chow over 4 weeks, safely reduced blood pressure. With a systolic and diastolic baseline blood pressure of respectively 191.5 (SE 4.3) and 143.1 (SE 4.1) mm Hg, GPA significantly reduced blood pressure compared to controls by 42.7 (5.5) systolic and 35.3 (4.8) mm Hg diastolic (*P* < 0.001), respectively [15]. To our knowledge, there are no human data on the safety and effects of this potential new antihypertensive agent; we will assess the tolerability of GPA in healthy volunteers.

## Methods/Design

### Test product

#### *GPA*

GPA or N-(aminoiminomethyl)-beta-alanine; (Cq_4_H_9_N_3_O_2_), is a structural isomer of creatine (Figure 1) [16]. GPA is generated *in vivo* via transamidination of β-alanine (Figure 2) [17-19]. The physiological concentration in human plasma is reported to range from trace amounts to 1.40 μmol/L [20,21]. Clearance is probably renal, akin to creatine, creatinine, and other guanidino compounds [17,19-21].

**Figure 1 Fig1:**
[figure not shown]
**Structural analogy between creatine and beta-guanidinopropionic acid.** Legend: Creatine **(a)** and beta-guanidinopropionic acid **(b)** have an identical molecular formula (C_4_H_9_N_3_O_2_)_,_ but creatine is methylated on its tertiary nitrogen, while in beta-guanidinopropionic acid, the methyl group is positioned in the carbon chain [16].

**Figure 2 Fig2:**
[figure not shown]
**Pathways of guanidino compound synthesis.** Legend: Guanidino compounds such as beta-guanidinopropionic acid, creatine, guanidinoacetic acid, gamma-guanidinobutyric acid, and guanidinosuccinic acid, are reported to be synthesized via transamidination of the amidino group from arginine as the major pathway, or through the urea cycle. Creatine biosynthesis involves two sequential steps catalyzed by L-arginine:glycine amidinotransferase (AGAT), and S-adenosylmethionine:guanidinoacetate N-methyltransferase (GAMT) After [17-19].

Despite the lack of human data on efficacy and side effects, GPA is available as a food-supplement, usually in doses of 500 mg, and is used by sportspersons to induce endurance capacity and promote weight loss [16]. GPA acts as a competitive inhibitor of cellular creatine uptake, and attenuates the flux through the cytoplasmic creatine kinase reaction [15,16,18]. CK catalyses the rapid and reversible transfer of a phosphoryl group from creatine phosphate to ADP, thereby forming creatine and ATP:$$ ADP+ creatine\kern0.5em  phosphate\kern0.5em <=>\kern0.5em ATP+ creatine. $$

The flux through the CK reaction is linearly correlated to the concentration of creatine [22].

Nuclear genes encode four CK subunits or monomers: cytoplasmic muscle (CKM), cytoplasmic brain (CKB), ubiquitous mitochondrial (CKMT1), and sarcomeric mitochondrial (CKMT2). The enzymatic functional form can be either a homodimer (BB and MM), a heterodimer (MB), or an octamer (mitochondrial monomers), thus creating five isoenzymes. The three dimeric cytoplasmic CKMM, CKMB, and CKBB isoenzymes are predominantly expressed in striated skeletal and heart muscle (MM), heart muscle (MB); and brain and smooth muscle (BB). The two octameric mitochondrial CK isoenzymes are expressed in striated muscle and other tissue [13]. The cytoplasmic isoenzymes appear in plasma of healthy subjects, due to what is thought to be a nontraumatic proportional release from tissue entering the bloodstream through the lymphatic system [6]. Hence, plasma CK is mainly the CKMM isoenzyme.

GPA is thought to inhibit cytoplasmic, but not mitochondrial CK [15,16,18]. Although GPA is phosphorylated by cytoplasmic CK, both GPA and phosphorylated GPA are 'inefficient substrates' for the CK reaction: *in vitro* Vmax values are <1% of the Vmax values of creatine and phosphocreatine [16,18,23]. Therefore, GPA may modulate the energy status of tissues, and we speculated that this creatine analog may reduce blood pressure.

In animal studies, supplemental GPA (1 to 3%) in the diet led to skeletal muscle changes similar to the adaptations of endurance training [16]. In the unstressed heart, left ventricular systolic pressure, cardiac output, and rate of tension development were unchanged with GPA. During high workload, studies showed unchanged or reduced peak left ventricular-developed pressure and cardiac output. However, blood pressure and peripheral hemodynamic parameters were not an outcome in these studies [16]. We recently showed that feeding 16-week-old spontaneously hypertensive rats a diet containing 3% GPA reduced blood pressure [15]. Importantly, the animals appeared healthy after GPA [15,16], and the blood pressure-lowering effect was reversible after withdrawal of the analog [15].

### Manufacturing and testing

In accord with the definition for food supplements in the legislation of the European Union [24], we consider GPA as well as creatine to be food supplements, because both are naturally occurring amino-acids. GPA is a white crystalline tasteless powder, soluble in water. GPA powder is ordered at Sequoia (Sequoia Research Products, Oxford, UK). There are no reports or bans on this product or the company to our knowledge, presented on the FDA website using the FDA search engine, or online with search engine Google, as of 20 February 2014. GPA, creatine, and identical placebo capsules will be manufactured by the Pharmacy & Pharmacology Department of the Slotervaart Hospital, Amsterdam, The Netherlands. This department is GMP certificated (ISO 9001:2001). Product dossiers for GPA and creatine were written and have received formal ethical approval by the AMC Amsterdam Medical Ethics Review Committee (MERC). GPA is marketed for human use in the U.S. and Australia, but not in European countries. According to the legal guidelines of the European Union, criteria of international organs, generally accepted criteria, or national criteria are approved when a supplement is not listed in the legislation of the European Union.

Following the U.S. FDA guidelines [25], we first qualified the supplier by establishing the reliability of the supplier, with the methods mentioned above. Next, the substance was tested for purity and for cyanide compounds. Cyanide was not expected to be quantifiable [26]. However, the cyano-group in cyanamide, one of the compounds used in the formation of GPA, provides a possible source of cyanide. We established in our certified tests a purity of more than 99% (detection limit) and a cyanide level lower than 1 p.p.m. (detection limit). Cyanide occurs in many food items, with high concentrations in cassava roots, almonds, and apricot kernels, up to 7,000 mg/kg (7 parts per thousand) [27].

In Europe, Annex II of Directive 88/388/EEC on flavorings sets the following maximum levels for hydrocyanic acid in foodstuffs and beverages: 1 mg/kg in food or beverages, with the exception of 50 mg/kg in nougat, marzipan or similar products, and 5 mg/kg in canned stone fruit [28]. With 100 mg GPA containing <1 p.p.m. cyanide, the contribution to the daily intake will be <0.1 microgram/day.

